#### Safety analyses

Based on the potential relationship between acupuncture and adverse events, adverse events are categorized as treatment-related or not. Acupuncture-related adverse events will be summarized by group and compared using a chi-square test (or Fisher’s exact test).

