## Methods/design

### Study design

This three-arm randomized sham-controlled trial has been approved by the ethics committees at each of the nine participating hospitals. Eligible KOA participants, diagnosed according to the American College of Rheumatology criteria [19], are randomly assigned (1:1:1) to receive 24 sessions of EA, MA, or SA over 8 weeks. The block randomization, with block sizes of 6 and 9, is stratified by study center and is performed via a web-based randomization system. Superficial insertion at non-acupoints with no electric current will be used for the SA group, which is one of the most commonly used approaches for administering sham treatments in acupuncture trials. The nature of acupuncture means that acupuncturists are not blinded to treatment allocation; however, patients, outcome assessors, and statisticians will remain masked. Informed consent will be obtained from each participant before randomization. The trial has been registered with ClinicalTrials.gov (NCT03366363).

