#### Safety outcome

Adverse events are recorded throughout the trial. Based on the potential relationship between acupuncture and adverse events, adverse events are categorized as related to the treatment or not.

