### Statistical analysis

#### Statistical analysis population

A modified full analysis set, a per-protocol set, and a safety set will be used in this trial. The modified full analysis set will consist of all randomized participants who have at least one post-baseline measurement according to the modified intention-to-treat principle. The modified full analysis set will be the primary analysis set, and all analyses will be conducted for this population if not otherwise stated. Analyses of the modified full analysis set will provide an estimate of the effects of EA and MA.

The per-protocol set will include those who complete the treatment and follow-up on time according to the protocol without major violations. Major violations of the protocol will be judged during the blinded audit of the data. They include but are not limited to not meeting the inclusion criteria, meeting the exclusion criteria, receiving other treatments that might affect the symptoms of KOA during the trial, and completing <20 sessions of acupuncture. The per-protocol set will be the secondary analysis set and will be used for the sensitivity analyses.

All those who are randomized and have received at least one session of acupuncture will be defined as the safety set, which is used for the safety analyses.

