#### General analysis principles

All data will be summarized by treatment group. Numbers (percentages) will be used to describe categorical data. Either means (standard deviations) or medians (interquartile ranges) will be used for quantitative data depending on whether the variables are normally distributed. If not otherwise stated, the significance level will be set at 0.05. The Bonferroni method will be used to adjust the significance level for multiple comparisons for the primary outcome. The conclusions will be based on the analysis of the primary outcome, and all secondary outcomes will be analyzed to support the primary analysis. All analyses will be carried out using SAS 9.3 (Cary, NC).

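### The only safety comparison specified is limited to events judged acupuncture-related; no between-arm comparison of all adverse events is planned

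*SAP article*

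**What the plan says.** Under Safety outcome, the SAP article collects everything: "Adverse events are recorded throughout the trial". In the same place, "adverse events are categorized as related to the treatment or not". It does not say who makes that classification.

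The Safety analyses section repeats the classification and then gives its only analysis instruction: "Acupuncture-related adverse events will be summarized by group and compared using a chi-square test", with Fisher's exact test as the alternative. Table 2, the shell for outcomes, has no safety rows.

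Three other statements bear on the point:
- Statistical analysis population: "All those who are randomized and have received at least one session of acupuncture will be defined as the safety set".
- General analysis principles: "All data will be summarized by treatment group", and for tests, "If not otherwise stated, the significance level will be set at 0.05".
- Study design: "acupuncturists are not blinded to treatment allocation", whereas "patients, outcome assessors, and statisticians will remain masked".

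**The concern.** Randomization protects a comparison of all adverse events by arm, because that comparison needs nobody's opinion on cause. A comparison restricted to events judged related loses this protection: an event must first pass a judgement made after treatment starts, and the judgement need not work the same way in each arm.

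Two different errors can follow. A real excess of events in an acupuncture arm may be weakened or missed if many of those events are not recognised as due to needling. Conversely, arms with the same event rate may appear to differ because a larger share of events is attributed to treatment in one of them. The first error does not depend on who makes the judgement. The second requires attribution to differ by arm, which is possible here because the sham is superficial needling without current and because some trial staff know the allocation.

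What is at stake is the safety conclusion. The primary efficacy analysis is unaffected.

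**Working it through.** **Setting the sections side by side.** Collection covers all events. The specific safety rule names related events only, for both the summary and the test. The general rule would support a descriptive table of all events by arm, but it adds no comparison. So one between-group safety comparison is specified, and it is on the related subset.

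**Inputs from the article.** The Sample size section gives 128 per group and 20% loss: 128 / (1 − 0.20) = 160 per arm, and 3 × 160 = 480, the stated total. The default level of 0.05 applies to the safety test. The article states no safety figure to reproduce.

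**Assumptions.** All 160 per arm enter the safety set. One acupuncture arm is compared with SA; the article does not say whether the safety test is pairwise. All event rates and attribution shares below are assumed.

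**Formula.** Related rate = all-event rate × share called related. The test is the uncorrected two-proportion Z-test (equivalent to the pairwise chi-square), Z = (p̂₁ − p̂₂) / √(2p̄(1 − p̄)/n), with p̄ the pooled proportion and n = 160. The probability of |Z| > 1.96 comes from exact binomial enumeration. As a hand check by the normal approximation for 20% vs 10%: p̄ = 0.15, null SE = √(2 × 0.15 × 0.85/160) = 0.0399, alternative SE = √((0.16 + 0.09)/160) = 0.0395, and (0.10 − 1.96 × 0.0399)/0.0395 = 0.55, so power is about 0.71.

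**(a) A real excess in all events, 20% vs 10%**

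| Share called related, both arms | Rates compared | Power |
|---|---|---|
| all events counted | 20% vs 10% | 71% |
| 50% | 10% vs 5% | 39% |
| 30% | 6% vs 3% | 25% |

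**(b) No difference in all events, 15% in both arms**

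| Share called related, acupuncture vs SA | Rates compared | Significant trials |
|---|---|---|
| 50% vs 40% | 7.5% vs 6.0% | 8% |
| 50% vs 30% | 7.5% vs 4.5% | 20% |
| 60% vs 20% | 9% vs 3% | 63% |

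The last case falls to 54% with Fisher's exact test, which the article also allows.

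**(c) Where restriction does not cost power.** If attribution favours the arm with the true excess, the related-only test gains power. With all events 20% vs 10% and shares of 80% vs 30%, the rates compared are 16% vs 3% and power is about 98% (normal approximation). The restriction can therefore move the result in either direction, depending on a quantity that the plan does not control.

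**The case against.** The strongest reply is that the general principles already require all data to be summarized by arm. Adverse events are recorded data, and nothing in the Safety analyses section excludes other events from a table. This stands in part. A reader might infer that a difference in all events could never appear in the results, and the documents do not support that: a descriptive table is permitted and arguably expected. But the rule is generic, while the section written for safety names related events alone. An analyst could follow that section without producing the wider table, and on any reading no comparison of all events is specified.

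A second stronger reading is that unblinded acupuncturists decide relatedness, so the comparison is biased. The documents do not say so. They name no assessor, they mask outcome assessors, and the protocol, which is not shown, may settle the matter. Unequal attribution is a risk here and not a stated fact. That sham needling would have fewer events attributed to it is likewise plausible but not documented.

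Third, the illustration rests on invented rates. That is true. The 63% comes from a threefold gap in attribution and is the high case; at 50% vs 40% the figure is 8%, close to nominal. Nor was the trial powered for safety, so 71% is a yardstick and not a target that the plan misses.

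Finally, testing related events is a legitimate question, and definitions and handling of serious events may sit in the protocol. Both are accepted. The objection here is to making the related subset the only specified comparison, not to analysing it or to any absent definition.

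**Conclusion.** The point holds in this form: the safety section specifies a summary and a test only for events judged acupuncture-related, all events by arm are covered at most by a generic descriptive rule, and the one stated safety comparison depends on the relatedness judgement.

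The size is uncertain because the article gives neither event rates nor attribution shares. On the assumptions above, restriction lowers power for a real excess from 71% to between 25% and 39% when attribution is equal across arms. With no real excess, unequal attribution makes the test significant in about 8% to 63% of trials. These are illustrations of what could happen, not predictions. The change is worth making because it needs only data already being collected and removes the dependence on a causal judgement from the main safety comparison.

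**What to change.** Amend the Safety analyses section before unblinding. In the safety set, summarize all adverse events and all serious adverse events by arm, regardless of relatedness. Give risk differences with 95% CIs for EA vs SA and MA vs SA, based on participants with at least one event. Keep treatment-related events as a subset table, with the existing test if wanted.

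The cost is one or two sentences, one more table from data already recorded, and a longer safety section.

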#### Blinding analyses

A kappa analysis will be used to determine whether participants correctly guessed their group assignment at a higher rate than would be expected by chance.

#### Additional analyses

Another three schemes to deal with any missing data for the primary outcome will be carried out to examine the robustness of the conclusion. First, any data missing at 8 weeks will be imputed using the last observation carried forward approach. Second, we will directly remove any missing data. Third, any data missing at 8 weeks will be imputed using multiple imputation [28]. By assuming the data missing are random, the missing data will be imputed using the Monte Carlo Markov chain method for multiple imputation with Proc MI (SAS). The initial seed will be set at 1000 and five datasets will be imputed. Any data missing for the primary outcome will be imputed by the observation value of age, gender, body mass index, Kellgren–Lawrence grade, and duration of disease. A subgroup analysis based on Kellgren–Lawrence grade will be performed.

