### Outcomes

#### Primary outcome

The primary outcome is the response rate [20], which is the proportion of patients who achieve the minimal clinically important improvement in pain and function at 8 weeks post-randomization. The average pain over the previous week will be assessed using an 11-point numerical rating scale (NRS) [21] with scores ranging from 0 to 10. The minimal clinically important improvement in pain is defined as 2 points in the NRS [11, 22]. The average function over the previous week is measured using the Western Ontario and McMaster Universities Osteoarthritis Index (WOMAC) function subscale [23] with scores ranging from 0 to 68. The minimal clinically important improvement in function is defined as 6 points in the WOMAC function subscale [11, 22]. The criteria for a participant to be a responder are presented in Fig. 1. The response rate is also measured at weeks 4, 16, and 26 after randomization.

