#### Analysis of the primary outcome

In the analysis of the primary outcome, the response rates of the three groups at 8 weeks will be calculated and the *Z*-test for comparisons of proportions will be used with the full analysis set. Any missing data at 8 weeks will be imputed using the baseline value. There will be two comparisons. The first comparison is that between the EA group and the SA group. The second is that between the MA group and the SA group. The significance level will be adjusted at 0.025 for multiple comparisons using the Bonferroni method.

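### The multiple-imputation sensitivity analysis uses a normal model with only five datasets for a yes/no outcome and gives no rule for deriving response

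*SAP article*

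**What the plan says.** The primary outcome (Outcomes, Primary outcome) is "the proportion of patients who achieve the minimal clinically important improvement in pain and function at 8 weeks post-randomization". It is built from two integer scores with fixed thresholds: "The minimal clinically important improvement in pain is defined as 2 points in the NRS", and 6 points for WOMAC function. For the main comparison, "the *Z*-test for comparisons of proportions will be used with the full analysis set", at 0.025 for each of EA vs. SA and MA vs. SA. The main missing-data rule in that section is "Any missing data at 8 weeks will be imputed using the baseline value".

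Under Additional analyses, three further schemes "will be carried out to examine the robustness of the conclusion": last observation carried forward, deletion, and multiple imputation. For the last, "the missing data will be imputed using the Monte Carlo Markov chain method for multiple imputation with Proc MI (SAS"). The plan also settles how many imputations are drawn and from what starting point: "The initial seed will be set at 1000 and five datasets will be imputed". Missing primary-outcome data are to be "imputed by the observation value of age, gender, body mass index, Kellgren–Lawrence grade, and duration of disease". The section does not say whether the responder flag or the two scores are imputed, or how an imputed value becomes a response.

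**The concern.** The MCMC method of PROC MI is a multivariate-normal method, whereas the outcome is binary and is analysed as a count of responders. The section is specific enough to fix the seed, yet it omits the step that links a normal draw to a response. Two analysts following it could therefore count different responders from the same data.

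Separately, five imputations leave visible random error in the pooled result when the plan itself allows for 20% loss. This is the only one of the three additional schemes that carries imputation uncertainty, so it is the one a reader would rely on to judge robustness to missing data.

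**Working it through.** **Inputs from the plan.** Assumed response EA 70%, MA 60%, SA 40%; two-sided level 0.025 (critical value 2.24); 80% power; 128 per arm; 20% loss; 480 in total; five imputations; thresholds 2 and 6 points.

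**The plan's own figure.** For 60% vs. 40%: [2.2414·√(2·0.5·0.5) + 0.8416·√(0.24 + 0.24)]² / 0.2² = 117.5, so 118 per arm. With the continuity correction, (n/4)·[1 + √(1 + 4/(0.2n))]² = 127.3, so 128. Then 128/0.8 = 160 per arm and 3 × 160 = 480. The figure reproduces. At 20% loss each arm has 128 observed and 32 missing.

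**Reading A: the flag is imputed.** With draws of mean p and SD s = √(p(1−p)), the share outside 0 to 1 is Φ(−p/s) + 1 − Φ((1−p)/s).
- p = 0.40 or 0.60: 0.207 + 0.110 = 31.7%.
- p = 0.70: 0.063 + 0.256 = 32.0%.

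Essentially no draw equals 0 or 1. Rounding at 0.5 turns 40/60/70% into 41.9/58.1/66.9%. The difference is little affected: with treatment arm in the imputation model, simulated mean differences were 0.191–0.205 unrounded and 0.194–0.208 rounded, against a true 0.20.

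**Reading B: the scores are imputed.** On an integer scale, a latent NRS improvement of 1.5 or more rounds to 2 and counts; an unrounded draw of 1.5 does not. The same applies at 5.5 for function. Assumptions, not from the plan: improvement SD 1.8–2.2 (NRS) and 9–11 (function), correlation 0.6, both thresholds required. Simulated response, imputed vs. observed: 32 vs. 40%, 44 vs. 51%, 54 vs. 60%, 58 vs. 65%. Imputed response is 6 to 8 points too low, or 0.2 × 6 to 0.2 × 8 = 1.2 to 1.6 points of an arm's rate at 20% missing. Rounding first closes the gap (50.7 vs. 50.9%). At SDs of 2 and 10 the shift was 6.4 to 7.0 points in every arm, so the difference moves by at most 0.2 × (7.0 − 6.4) = 0.12 points.

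**Monte Carlo error.** Illustrative data: 74/128 vs. 53/128 observed responders (57.8% vs. 41.4%, difference 0.164), imputed within arm, pooled by Rubin's rules.
- v = 0.578·0.422 + 0.414·0.586 = 0.4865.
- Within-imputation variance W = v/160 = 0.00304.
- Between-imputation variance B = 0.2²·v·(1/32 + 1/128) = 0.00076.
- With M = 5: T = W + 1.2B = 0.00395 and z = 0.164/√0.00395 = 2.61.
- Seed-to-seed SD of the pooled difference: √(B/5) = 0.0123, which adds 0.0123/0.0629 = 0.196 to the SD of z.
- B is estimated on 4 degrees of freedom (relative SD √(2/4) = 0.707), which adds 2.61·½·1.2·0.00076·0.707/0.00395 = 0.213.
- Combined: √(0.196² + 0.213²) = 0.29. Share of seeds below 2.24: Φ((2.24 − 2.61)/0.29) = about 10%.
- With M = 50 the same steps give z = 2.66 and SD √(0.063² + 0.055²) = 0.083; practically no seed falls below 2.24.

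Simulation agrees. M = 5: SD 0.28–0.29, 95% range about 2.06–3.17, 8 to 10% of seeds miss. M = 50: SD 0.083–0.085, range 2.49–2.83, none miss.

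**Where it fades, M = 5.** The same 16-point difference with 10% missing: 0.5% of seeds miss; with 5% missing: none. An observed 20-point difference with 20% missing and arm in the model: 0.1% in one simulation and about 1% in another. A 30-point difference: none.

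Averaged over simulated trials with true rates 60% vs. 40% and arm in the model, some of which land near the threshold by chance, two seeds gave opposite verdicts at M = 5 vs. M = 50 in 11.1% vs. 2.3% (20% missing), 5.6% vs. 1.1% (10%) and 1.1% vs. 0.0% (5%).

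**The case against.** The strongest reply has four parts.

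1. A reader might infer that the plan certainly imputes the yes/no flag and so produces invalid responses. The document does not say so. Its main rule fills gaps with the baseline value, which exists for the scores and not for the flag, so imputing scores and then deriving response is the more coherent reading. This stands. The firm finding is that the imputed variable and the conversion rule are unstated while the method and number of datasets are stated.
2. A reader might infer that the miscount biases the comparison. It does not to any useful degree: the shift is nearly the same in each arm and cancels in the tested difference. This stands.
3. A reader might infer that the seed could be chosen to suit the result. It is fixed at 1000 in advance, so the run is reproducible, and Rubin's rules allow for finite M through the (1 + 1/M) term. This stands too, but the reported result remains one draw from the seed-to-seed range above.
4. The 20% is an allowance for loss over a trial that follows patients to week 26, and participants with no post-baseline measurement leave the modified full analysis set. Week-8 missingness may well be lower, and the effect would shrink accordingly.

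One qualification runs the other way. The listed imputation variables do not include treatment arm. At 20% missing that alone shrinks a 20-point difference to about 0.8 × 20 = 16 points, which is the near-threshold case. With observed rates of 60.2% vs. 39.8% and the covariates as listed, 84% of seeds reached 0.025 at M = 5 and all did at M = 50. This is mainly the attenuation, a separate defect that more datasets would not cure.

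**Conclusion.** The concern holds in limited form. A normal-theory method and five datasets are stated for a binary outcome, with no rule for deriving response. On the flag reading the planned test cannot be run as written; on the score reading each arm's imputed response is understated by about 6 to 8 points, with little effect on the difference. Monte Carlo error matters when missingness is near 20% and the difference is near the 0.025 boundary (z SD about 0.28 and 8 to 10% of seeds missing, against about 0.08 and none with 50 datasets). It is close to nil in the same example at 5 to 10% missing, and at an observed 20-point difference when imputation respects treatment arm.

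The score-level figures rest on assumed SDs and correlation and on both thresholds being required; the responder figure was not available for this check. The 16-point dataset is illustrative, and 5% and 10% missing are assumed levels. A reader might infer that the trial's conclusion is at risk. It is not: the plan bases its conclusions on the primary outcome analysis, which uses baseline-value imputation and does not depend on this scheme.

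**What to change.** Under Additional analyses:
- Replace five datasets with at least 50.
- State which variable is imputed. Either impute week-8 responder status with a logistic model (PROC MI, FCS statement with LOGISTIC, responder as a CLASS variable), or impute the week-8 NRS and WOMAC function scores as valid integers (predictive mean matching or rounding) and then apply the responder rule.
- State that the EA−SA and MA−SA risk differences are combined by Rubin's rules and each tested at 0.025.

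The cost is a wording change, a little more computing, a check for sparse cells, and confirmation that the stated SAS release supports the chosen option. No further patients or data are needed. The choice of imputation covariates, in particular the absence of treatment arm, should be settled at the same time, because this change does not correct it.

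### The multiple-imputation check on the primary outcome omits treatment arm and the patient's own scores, so it shrinks the arm differences in step with the missing fraction

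*SAP article*

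**What the plan says.** The primary rule, under Analysis of the primary outcome, is: "Any missing data at 8 weeks will be imputed using the baseline value". A patient handled this way shows no change and so counts as a non-responder.

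Additional analyses then adds three alternatives: "Another three schemes to deal with any missing data for the primary outcome will be carried out to examine the robustness of the conclusion". They are last observation carried forward (LOCF), deletion of missing data (complete case), and multiple imputation. The third is introduced with "By assuming the data missing are random", and "the missing data will be imputed using the Monte Carlo Markov chain method for multiple imputation" in SAS. Its predictors are listed: "Any data missing for the primary outcome will be imputed by the observation value of age, gender, body mass index, Kellgren–Lawrence grade", with disease duration as the last item. The remaining settings are also fixed: "The initial seed will be set at 1000 and five datasets will be imputed".

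Arm is not on the list, and no section says that imputation runs separately by arm. Baseline NRS and WOMAC function (Table 1) and their values at weeks 4, 16 and 26 (Secondary outcomes) are collected but not listed. The modified full analysis set requires some measurement after baseline, so a patient in it who misses week 8 has data from another occasion.

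**The concern.** An imputation model that leaves out a variable used in the analysis assumes that this variable is unrelated to the missing values, given those that are included. Here the omitted variable is the contrast under test. The Sample size section itself assumes response of 70%, 60% and 40% in the EA, MA and SA groups, so the plan expects arm to matter a great deal. The five listed characteristics are balanced across arms on average by randomisation and cannot stand in for it.

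The patient's own scores matter for a second reason. Response is computed from change in NRS and WOMAC function, and a patient's absence at week 8 may depend on how that patient was doing at week 4. Without those scores, missing at random is harder to believe and precision is lost.

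What is at stake is how this sensitivity analysis can be read beside the primary result.

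**Working it through.** **Inputs.** Response 70/60/40%, two-sided alpha 0.025 per comparison, 80% power and 20% loss to follow-up (Sample size); 1:1:1 allocation (Study design). The documents give no week-8 missing rate, so 5%, 10% and 20% are assumed.

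**The plan's own figure.** For 60% against 40%, the pooled two-proportion formula gives 118 per group, and 128 with continuity correction, as stated. Then 128/(1−0.20) = 160 per arm, and 3 × 160 = 480. The planning figures reproduce.

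**Effect of omitting arm.** Let d be the fraction missing in each arm, equal across arms, with missing values drawn around the pooled observed rate.

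- Pooled rate = (0.70 + 0.60 + 0.40)/3 = 0.567.
- Expected rate in an arm = (1−d) × arm rate + d × pooled rate.
- The pooled term cancels in a difference, leaving (1−d) × true difference.

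At d = 0.20:

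- EA: 0.8 × 0.70 + 0.2 × 0.567 = 0.673
- MA: 0.8 × 0.60 + 0.2 × 0.567 = 0.593
- SA: 0.8 × 0.40 + 0.2 × 0.567 = 0.433
- MA–SA = 0.160 and EA–SA = 0.240

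| Missing (assumed) | MA–SA, true 20 | EA–SA, true 30 |
|---|---|---|
| 5% | 19 | 28.5 |
| 10% | 18 | 27 |
| 20% | 16 | 24 |

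**Comparison with the primary rule.** Counting missing patients as non-responders gives (1−d) × arm rate, so at d = 0.20 MA–SA = 0.48 − 0.32 = 0.16. This is the same as the multiple imputation.

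**Unequal missingness (assumed 10/10/30% for EA/MA/SA).** Pooled observed rate = (0.63 + 0.54 + 0.28)/(0.9 + 0.9 + 0.7) = 0.58. Multiple imputation: MA = 0.54 + 0.1 × 0.58 = 0.598, SA = 0.28 + 0.3 × 0.58 = 0.454, difference 0.144. Baseline value: 0.54 − 0.28 = 0.26. The truth is 0.20. The two analyses now disagree, and part of the gap comes from the imputation model.

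**Simulation.** 2,000 trials, 160 per arm, five imputations, a continuous score imputed and then dichotomised, and Rubin's rules. Assumed correlations: 0.2 for one covariate with the week-8 score, about 0.6 between week-4 and week-8 errors. Entries are MA–SA (true 0.20).

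| Imputation model | 20% missing completely at random | Missingness depends on week-4 score |
|---|---|---|
| As written | 0.160 | 0.152 |
| With arm | 0.199 | 0.197 |
| With arm and week-4 score | 0.200 | 0.201 |

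In the first column, simulated power for MA–SA is 67%, 85% and 88% respectively. Deletion gives 0.200 there. Omitting arm causes almost all of the shrinkage.

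**The case against.** The strongest reply is that this is one of three sensitivity schemes. It does not supply the primary estimate or P value, and General analysis principles ties the conclusions to the primary outcome analysis. LOCF and complete case do not use the model, and complete case is unbiased when data are missing completely at random. With equal missingness the bias runs toward no difference, so a positive result that survives is conservative support. All of this stands, and it limits the severity.

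The 20% is a planning rate for loss to follow-up, and follow-up runs to week 26. The primary set also excludes patients with no measurement after baseline. Week-8 missingness may therefore be well below 20%, and at 5% the cost on MA–SA is one point. This also stands.

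Three stronger readings are tempting, but the documents do not support them:

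- A reader might infer that the robustness of the primary result cannot be tested at all. Two other schemes remain, and the direction of this one's bias is known when missingness is equal.
- A reader might infer that a normal-theory method is being applied to a 0/1 response. The plan does not say that the response flag is imputed. The primary rule substitutes a baseline value, which exists for the scores but not for response, so imputing scores is the natural reading.
- A reader might infer that five datasets are too few. At a missing-information fraction of 0.20, relative efficiency is 1/(1 + 0.2/5) = 96%, and the seed is fixed. More would be a preference.

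It could also be said that an article condenses a fuller plan. But this article fixes the method, seed, number of datasets and predictors, and a programmer following it would leave arm out.

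**Conclusion.** The point holds as a should-fix. As written, the multiple imputation does not estimate the treatment effect under its own missing-at-random assumption, because it treats arm as irrelevant to the values it fills in. With equal missingness, agreement with the baseline-value primary analysis is partly built in, since both carry the same factor (1−d), and a loss of significance could be an artefact of the model.

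The size rests on the plan's assumed response rates and on a missing rate that it does not state; the loss is 1 to 4 points on MA–SA and 1.5 to 6 on EA–SA over the range shown. The simulated power figures also depend on the assumed correlations. The primary test is not affected.

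**What to change.** Rewrite the multiple-imputation paragraph under Additional analyses as follows:

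- State that the week-8 NRS and WOMAC function scores are imputed, separately by treatment arm or with arm in the model.
- Add baseline and other-visit NRS and WOMAC function scores to the five listed covariates.
- Derive response in each completed dataset, then combine the risk differences for EA–SA and MA–SA.

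Raising the number of imputations is optional. Every variable is already collected, so the cost is plan wording and SAS code. The article says that the plan was written before data collection ended, so such a change need not draw on results; a later change should be recorded as a dated amendment.
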